#### Withdrawal criteria

A participant will be withdrawn from the trial if any of the following conditions occur:

Post-enrolment identification of protocol ineligibility.Poor adherence that prevents compliance with the study schedule or procedures.Receipt of another investigational treatment within the previous 3 months.Emergence of serious adverse events or complications requiring discontinuation of the intervention.Voluntary withdrawal for personal, family, or social reasons that preclude completion of the treatment course.

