### Safety evaluation

Safety monitoring will focus on adverse events (AEs) related to EA, including vasovagal reactions (dizziness, nausea, pallor, transient hypotension or syncope), intolerable needling pain, local hematoma or bruising, bleeding, infection or abscess at needle sites, needle breakage, and other post-needling reactions. All AEs will be recorded on standardized case report forms, noting the onset of time, duration, severity, relationship to the intervention, actions taken, and outcome. Serious adverse events (SAEs) will be defined according to Good Clinical Practice. Participants with repeated vasovagal episodes, severe AEs, or any SAE judged related to the intervention will discontinue study treatment and may be withdrawn if further participation is unsafe. All SAEs will be reported to the principal investigator and the institutional ethics committee within 24 h and will be managed according to the Data and Safety Monitoring procedures of West China Hospital.

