### Clinical data analysis

Statistical analyses will be performed using IBM SPSS 26.0 (IBM, Armonk, NY, USA). The primary efficacy analyses will follow the intention-to-treat (ITT) principle (35), including all randomized participants analyzed according to their allocated group, irrespective of treatment adherence. A per-protocol (PP) population will be defined as participants who complete at least 16 of the 20 planned treatment sessions (≥80% adherence) and have the primary endpoint (week-4 MoCA) assessed. For the MRI substudy, the PP set will include participants with analyzable QSM data at both baseline and week 4.

MoCA change from baseline to week 4 will be the sole primary endpoint, and hypothesis testing for this outcome will use a two-sided significance level of 0.05. Prespecified secondary clinical outcomes (MMSE, MBI, HAMA, HAMD, PSQI, and PSCI incidence) will be analyzed without formal adjustment for multiplicity and will be interpreted as exploratory. For these endpoints, we will report effect sizes with 95% confidence intervals and regard *p*-values as descriptive, in order to avoid over-interpretation of nominal statistical significance in this pilot trial. Multiplicity for imaging analyses across QSM regions of interest will be controlled using false-discovery-rate correction as described below.

For the primary endpoint (change in MoCA from baseline to week 4), if missing data at week 4 exceeds 5% of randomized participants, multiple imputation under a missing-at-random assumption will be used as the main ITT analysis (36, 37). For secondary outcomes, analyses will primarily use available cases, and sensitivity analyses with multiple imputation may be conducted if missingness is substantial. Reasons for missing data will be documented wherever possible.

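### The withdrawal rules do not separate stopping treatment from leaving follow-up, which conflicts with the intention-to-treat and safety sections and puts outcome data at risk

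*Protocol article*

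**What the plan says.** Three sections of the protocol article bear on this.

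- **Withdrawal criteria.** The rule is mandatory and concerns the trial, not only the treatment: "A participant will be withdrawn from the trial if any of the following conditions occur". Three of its five triggers matter most here: "Post-enrolment identification of protocol ineligibility", "Poor adherence that prevents compliance with the study schedule or procedures" and "Emergence of serious adverse events or complications requiring discontinuation of the intervention". A fourth concerns receipt of another investigational treatment in a preceding three-month window, with no stated reference date. The section does not say whether outcomes are still collected afterwards.
- **Safety evaluation.** Participants with repeated vasovagal episodes, severe adverse events or a related serious adverse event "will discontinue study treatment and may be withdrawn if further participation is unsafe". Stopping treatment and withdrawal are two steps here, and the second is discretionary.
- **Clinical data analysis.** The primary analysis is by intention to treat, "including all randomized participants analyzed according to their allocated group, irrespective of treatment adherence". The per-protocol set requires 16 of the 20 sessions and a week-4 MoCA. For the primary endpoint, "if missing data at week 4 exceeds 5% of randomized participants", multiple imputation assuming data missing at random becomes the main analysis. Secondary outcomes primarily use available cases.

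Table 1 already schedules MoCA at week 4 and at 3 months after onset.

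**The concern.** Site staff cannot follow all three sections as written. One ends trial participation for poor adherence, another needs the outcomes of poor adherers, and the third leaves withdrawal after stopping treatment to judgement.

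If the withdrawal rule is followed literally, outcomes are lost because of events after randomisation. Those events may be related to prognosis, and they may differ by arm. The EA arm has deeper needling, manipulation to elicit deqi and a 1–2 mA current; the sham arm has needling to 0.3 cun with no manipulation and no current. The adherence trigger has no session threshold, the article does not say who applies it, and the treating acupuncturists know the allocation. Missing at random is least secure for participants lost in this way, and an outcome that was never measured cannot be recovered by any later analysis plan.

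**Working it through.** **The sections side by side**

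| Event | Withdrawal criteria | Other section |
|---|---|---|
| Poor adherence | Withdrawn from the trial (mandatory) | Clinical data analysis: analysed regardless of adherence |
| Ineligibility found later | Withdrawn from the trial (mandatory) | Clinical data analysis: all randomised are analysed |
| Serious event or complication that stops the intervention | Withdrawn from the trial (mandatory) | Safety evaluation: for severe events or related serious events, treatment stops and withdrawal is optional |

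The per-protocol definition points the same way. Its session criterion does separate work from its week-4 MoCA criterion only if some participants with fewer than 16 sessions are still assessed. The analysis section therefore presupposes that at least some poor adherers stay in follow-up.

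**Scale of missing data**

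Inputs from Sample size: 30 per arm targeted, 20% attrition, 36 per arm enrolled (72 in total).

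- The plan's figure reproduces as 30 × 1.20 = 36. Dividing instead gives 30 / 0.80 = 37.5, so 38. That is a separate minor matter, and nothing below depends on it.
- Expected loss at 20%: 0.20 × 36 = 7.2 per arm, or 14.4 of 72.
- Imputation trigger: 0.05 × 72 = 3.6, so 4 or more missing.
- Binomial probability of 4 or more missing among 72: 0.49 if the true missing rate is 5%, 0.94 at 10%, and above 0.999 at 20%.

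At the plan's own attrition, missing-at-random imputation would almost certainly be the main primary analysis.

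**Possible bias (the documents give no gap and no difference in rates; both are assumed)**

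Let w be the share of an arm withdrawn, and g the amount by which withdrawn participants fall short of what the imputation predicts.

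- Error in an arm mean = w × g.
- Error in the contrast = (w × g in EA) − (w × g in sham).

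| Assumption | Result |
|---|---|
| w = 0.20, all due to these rules; g = 1 to 3 MoCA points, one arm only | 0.20 × 1 = 0.2 to 0.20 × 3 = 0.6 points |
| As above, but only half of the attrition due to these rules (w = 0.10) | 0.1 to 0.3 points |
| w = 0.30 against 0.10; g = 0.25 to 1.0 SD in both arms | (0.30 − 0.10) × g = 0.05 to 0.20 SD |
| Same w and same g in both arms | 0 |

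For scale, with 28.8 per arm observed (36 × 0.80), the standard error of a difference in means is √(2/28.8) = 0.26 SD. The third row stays below one standard error.

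**The case against.** A reader might infer that the withdrawal rules defeat the intention-to-treat analysis. The text does not support that: every randomised participant stays in the analysis set, and missing week-4 MoCA values are imputed above the 5% threshold. What is at risk is observed data, not membership.

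Other objections also carry weight:

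- No section says outright that assessments end at withdrawal. That is the natural reading of leaving the trial, but it is an inference, and the full protocol may say more.
- The triggers are narrower than poor adherence or adverse events in general. Adherence must be poor enough to prevent following the schedule or procedures, and some of those participants could not be assessed under any wording. The adverse-event trigger covers serious events or complications that stop the intervention, which may be few.
- The 20% is total anticipated attrition and would include voluntary withdrawal and ordinary loss to follow-up. Only part of it could be avoided by rewording.
- A reader might take the item on another investigational treatment as a baseline fact, and so a misplaced exclusion criterion. Its three-month window has no anchor. Counted back from a later visit, it would cover treatment taken during the trial.
- The article calls the trial exploratory and a pilot.

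These points limit the size and certainty of the concern. They do not remove the conflict between the sections. The trial's exploratory status does not settle the matter either, because its stated purpose is to estimate effect sizes, and those estimates are what the missing outcomes would distort.

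**Conclusion.** The point holds as a conflict between stated rules. Withdrawal criteria require exit from the trial for reasons that Clinical data analysis says should not affect inclusion, and make automatic what Safety evaluation leaves to judgement. Followed as written, and on the reading that withdrawal ends assessment, the rules replace observed outcomes with a missing-at-random assumption for the primary endpoint and primarily with available cases for secondary outcomes.

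The worst case is an error of 0.2 to 0.6 MoCA points in one arm's mean. It requires all of the 20% attrition to come from these rules, a shortfall of 1 to 3 points confined to one arm, and imputation that recovers none of it. Smaller shares scale down in proportion, and the bias in the contrast is near zero if rate and mechanism match across arms. Informative and differential missingness is plausible here but not shown by any figure in the document.

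**What to change.** Reconcile Withdrawal criteria, Safety evaluation and Clinical data analysis:

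1. Define discontinuation of the intervention and withdrawal from follow-up as two separate events.
2. State that the week-4 and 3-month MoCA assessments already in Table 1 are still collected for all randomised participants, including those later found ineligible or poorly adherent. The exceptions are withdrawal of consent to follow-up and the safety judgement already described in Safety evaluation.
3. State the reference date for the item on another investigational treatment. If it means before enrolment, list it under Exclusion criteria; if it means during the trial, say so.

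None of this addresses when treatment is stopped. The cost is protocol wording and a small effort to complete already scheduled assessments in participants who stop treatment. It should be done before anyone is withdrawn under the present wording, because outcomes not collected cannot be recovered.

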### Sample size

This exploratory trial was primarily designed to estimate effect sizes and assess protocol feasibility. Consistent with pilot-trial recommendations for acupuncture and traditional Chinese medicine (22, 23), we set the target sample size at 30 participants per arm. Allowing for an anticipated 20% attrition, we therefore planned to enroll 36 participants in each group (total *n* = 72). For the MRI substudy, we will randomly select 15 participants per arm (*n* = 30) from the clinical cohorts, in line with Desmond and Glover’s guidance on imaging sample sizes (24). Under a two-tailed *α* = 0.05, this total sample provides approximately 80% power to detect medium-to-large correlations (r ≥ 0.50) between QSM-derived susceptibility measures and cognitive outcomes, based on Fisher’s z transformation in G*Power 3.1. Smaller associations will be interpreted with caution, and the MRI substudy is therefore primarily intended to provide preliminary estimates of effect sizes and variance components to guide the design of future, adequately powered imaging trials. With 15 participants per arm, the substudy will also have approximately 80% power to detect between-group differences in 4-week changes in regional susceptibility of approximately 0.8 standard deviations (Cohen’s d), whereas smaller treatment effects on QSM will be treated as exploratory and described descriptively.

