### Outcome measures

#### Primary outcome measurement

The primary outcome is the change in MoCA scores from baseline to the end of the 4-week treatment period. This time point corresponds to completion of the EA course and the early subacute rehabilitation phase, when treatment intensity and neuroplastic potential are highest and short-term clinical decision-making is often made. MoCA is a validated screening tool for global cognitive function, covering seven domains: visuospatial/executive function, naming, attention, language, abstraction, delayed recall, and orientation (total score = 30). Using the standardized cutoff of <26 established for cognitive impairment detection, lower scores denote greater severity of cognitive dysfunction (29). To address longer-term clinical relevance, MoCA will also be reassessed at 3 months after stroke onset, and PSCI incidence at 3 months will be analyzed as a key secondary outcome.

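### After a treatment-related SAE, the safety section stops treatment and leaves withdrawal optional, but the withdrawal criteria then make exit from the trial compulsory

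*Protocol article*

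**What the plan says.** The list under Withdrawal criteria opens with a compulsory rule: "A participant will be withdrawn from the trial if any of the following conditions occur". One of its conditions is "Emergence of serious adverse events or complications requiring discontinuation of the intervention".

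Safety evaluation covers related events separately: "Participants with repeated vasovagal episodes, severe AEs, or any SAE judged related to the intervention will discontinue study treatment". The same sentence makes leaving the trial discretionary. Its wording for the SAE case is "any SAE judged related to the intervention will discontinue study treatment and may be withdrawn if further participation is unsafe".

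On analysis, Clinical data analysis states: "The primary efficacy analyses will follow the intention-to-treat (ITT) principle", "including all randomized participants analyzed according to their allocated group, irrespective of treatment adherence". The week-4 MoCA change is the sole primary endpoint. MoCA is repeated 3 months after onset, and "PSCI incidence at 3 months will be analyzed as a key secondary outcome". Table 1 schedules both assessments for all 72 participants.

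**The concern.** Stopping treatment and leaving the trial are different events, and Safety evaluation itself keeps them apart. The withdrawal list merges them for SAEs: once the intervention has to stop, the participant leaves the trial. Staff handling a related SAE in someone who is fit and willing to be assessed would find one section that permits continued follow-up and another that forbids it. The article does not say which section prevails.

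At stake is outcome data. If staff take withdrawal from the trial to mean no further assessments, the week-4 and 3-month MoCA scores are lost for a reason tied to the assigned treatment. An analysis meant to disregard adherence is best served by observed outcomes in people who stop treatment, and the literal withdrawal rule can remove them.

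**Working it through.** **Comparing the two rules for one event, a related SAE**

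1. Safety evaluation: treatment must stop.
2. Withdrawal criteria: an SAE that requires the intervention to stop is a listed condition. Step 1 satisfies it.
3. Withdrawal criteria: any listed condition means compulsory exit from the trial.
4. Safety evaluation, same participant: exit is optional and depends on whether continuing is unsafe.

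Steps 3 and 4 disagree whenever the participant can safely continue. The result does not depend on how the withdrawal item is parsed. If the need to discontinue qualifies both SAEs and complications, a related SAE meets it through step 1. If it qualifies complications only, every SAE is covered, related ones included.

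**Size**

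The article has no figure to reproduce here, because it gives no rate of related SAEs, no SD of MoCA change and no outcome for such participants. The following is illustration only.

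Inputs from the article: 72 participants, 36 per arm; target 30 per arm; 20% attrition ("Allowing for an anticipated 20% attrition, we therefore planned to enroll 36 participants in each group").

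Assumed inputs: k = 0 to 2 affected participants, all in one arm; a true week-4 change that differs from the imputed one by d = 2 to 5 MoCA points; SD of change 3 to 4 points.

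- Share of the sample: 1/72 = 1.4%; 2/72 = 2.8%.
- Share of planned losses, taking 20% of 72 = 14.4: 1/14.4 = 6.9%; 2/14.4 = 13.9%.
- Share of planned losses, taking the allowance actually built in, 2 × (36 − 30) = 12: 1/12 = 8.3%; 2/12 = 16.7%.
- Shift in the arm mean, k × d / 36:
  - k = 0: none
  - k = 1: 2/36 = 0.06 to 5/36 = 0.14 points
  - k = 2: 4/36 = 0.11 to 10/36 = 0.28 points
- Standard error of the group difference, SD × √(2/36): 3 × 0.2357 = 0.71; 4 × 0.2357 = 0.94.
- Shift relative to the standard error, for k = 1 or 2: lowest 0.056/0.943 = 0.06; highest 0.278/0.707 = 0.39.

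Putting every case in one arm, and treating every case as otherwise assessable, makes the upper end a worst case within these assumptions.

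**The case against.** Four arguments stand against the point.

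*The sections can be read together.* Safety evaluation could be taken as the specific rule and the withdrawal list as a general summary. That is a sensible working solution, but nothing in the article says so, and the list is worded as compulsory. Reading exit from the trial as exit from treatment does not help either, since Safety evaluation uses the two as distinct steps.

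*Intention-to-treat is not broken.* A reader might infer that compulsory withdrawal contradicts the intention-to-treat statement. It does not. All randomized participants stay in the analysis set, and multiple imputation becomes the main analysis if more than 5% of week-4 MoCA values are missing. Only the observed value may be lost. This objection stands in full, so no contradiction with the analysis population is claimed.

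*The loss of data depends on an unstated step.* The article neither says nor rules out that withdrawn participants are still assessed, and a condensed article may leave that to the full protocol. So the data loss is conditional, and the silence is not itself the point. What remains is that two stated rules disagree, which does not depend on missing detail.

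*Few participants are involved.* The needling reactions listed under Safety evaluation are mostly minor, related SAEs may be zero, and poor adherence is a likelier route to withdrawal. This also stands, and it limits the weight of the point.

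A reader might also extend the conflict to unrelated SAEs. The article does not support that: Safety evaluation sets no discontinuation or withdrawal rule for them, so there is nothing for the withdrawal list to contradict.

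**Conclusion.** The inconsistency is real but minor. For a related SAE in a participant who can safely be followed, Safety evaluation permits continued participation and Withdrawal criteria require exit. This follows from the text alone and needs no assumption.

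The consequence does rest on assumptions. If withdrawal ends assessments, and if 1 or 2 participants are affected, the arm mean might move by 0.06 to 0.28 MoCA points, or 0.06 to 0.39 of a standard error. With no such event there is no effect. It would be an overreading to infer that the primary result is materially biased: the number of events, the deviation from the imputed value and the SD are all assumed, and no conclusion is shown to change. The point is worth acting on because the correction is easy, not because the expected effect is large.

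**What to change.** Reword the SAE and complication item under Withdrawal criteria so that it leads to discontinuation of study treatment instead of withdrawal from the trial. Add that the week-4 and 3-month assessments already in Table 1 are kept unless the participant withdraws consent or continuing would be unsafe.

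The edit reaches further than the conflict. The item is not limited to related events, so unrelated SAEs and complications that force a treatment stop would also move from compulsory exit to treatment discontinuation with follow-up. That is acceptable because the safety exception is retained, but it should be a deliberate choice. The other withdrawal items, such as poor adherence and ineligibility found after enrolment, are unchanged.

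The cost is one reworded item and a few already scheduled assessments in participants who have stopped treatment. No new visit is needed.

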### Sample size

This exploratory trial was primarily designed to estimate effect sizes and assess protocol feasibility. Consistent with pilot-trial recommendations for acupuncture and traditional Chinese medicine (22, 23), we set the target sample size at 30 participants per arm. Allowing for an anticipated 20% attrition, we therefore planned to enroll 36 participants in each group (total *n* = 72). For the MRI substudy, we will randomly select 15 participants per arm (*n* = 30) from the clinical cohorts, in line with Desmond and Glover’s guidance on imaging sample sizes (24). Under a two-tailed *α* = 0.05, this total sample provides approximately 80% power to detect medium-to-large correlations (r ≥ 0.50) between QSM-derived susceptibility measures and cognitive outcomes, based on Fisher’s z transformation in G*Power 3.1. Smaller associations will be interpreted with caution, and the MRI substudy is therefore primarily intended to provide preliminary estimates of effect sizes and variance components to guide the design of future, adequately powered imaging trials. With 15 participants per arm, the substudy will also have approximately 80% power to detect between-group differences in 4-week changes in regional susceptibility of approximately 0.8 standard deviations (Cohen’s d), whereas smaller treatment effects on QSM will be treated as exploratory and described descriptively.

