## Methods

### Research design

This single-blind, RCT will be conducted in the Department of Rehabilitation Medicine, West China Hospital of Sichuan University (Chengdu, China). A total of 72 inpatients with IS-CI will be randomized 1:1 to receive EA or sham electroacupuncture (sEA). Figure 1 outlines the study flow, and Table 1 details the schedule of enrolment, interventions, and assessments.

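### Enrolling 36 per arm leaves about 29, not the target of 30, at the stated 20% attrition

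*Protocol article*

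**What the plan says.** The Sample size section describes an exploratory trial meant mainly to estimate effect sizes and assess feasibility. It gives no power calculation for the main comparison. The size rests on convention: "Consistent with pilot-trial recommendations for acupuncture and traditional Chinese medicine (22, 23"), "we set the target sample size at 30 participants per arm". The next sentence makes the allowance for loss: "Allowing for an anticipated 20% attrition, we therefore planned to enroll 36 participants in each group", 72 in total.

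The total of 72 recurs in the Abstract, in Table 1 and under Research design ("A total of 72 inpatients with IS-CI will be randomized 1:1"). No other section gives a different attrition rate or a different number expected to complete.

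**The concern.** The three figures are joined by a *therefore*: 30 wanted, 20% lost, so 36 enrolled. An attrition rate is normally a share of those enrolled, so the number to enrol is the target divided by the proportion retained. Multiplying the target by one plus the rate gives too few, and the gap widens as the rate rises. The figure of 36 looks like the result of that multiplication.

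At stake is whether the plan delivers its own target. The 30 per arm is the only justification offered for the size of the main trial. In a trial meant to inform feasibility, the number expected to remain is one of the planning figures a reader will use.

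**Working it through.** **Inputs**, all from the Sample size section: target 30 per arm; attrition 20%; enrolment 36 per arm, 72 in total. Allocation is 1:1 (Research design).

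**Reproducing the plan's figure.** No formula is stated. Multiplying the target by one plus the rate gives 30 × (1 + 0.20) = 36.0, which matches exactly. Dividing by the proportion retained gives 30 / (1 − 0.20) = 37.5, rounded up to 38, which does not match.

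**What 36 per arm leaves.**
- Per arm: 36 × 0.80 = 28.8, which is 1.2 below 30.
- In total: 72 × 0.80 = 57.6, which is 2.4 below 60.

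**What 30 per arm needs at 20% attrition.** 38 per arm, 76 in total (38 × 0.80 = 30.4 retained per arm). Working on the total instead gives 60 / 0.80 = 75.

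**The attrition at which 36 is enough.** (36 − 30) / 36 = 6/36 = 16.7%.

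**How likely the target is to be met.** Assume, beyond the document, that each participant completes independently with probability 0.80. The binomial probability of at least 30 completers is then:

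| Enrolled per arm | One given arm | Both arms |
|---|---|---|
| 36 | 0.40 | 0.40² = 0.16 |
| 38 | 0.66 | 0.66² = 0.43 |

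**Effect on precision, for illustration only.** The protocol makes no power statement for the MoCA comparison. For an unadjusted two-sample t-test in completers, two-sided α = 0.05 and 80% power, the detectable standardised difference is 0.736 at 30 per arm and 0.751 at 28.8 per arm. The change is 0.751 / 0.736 − 1, about 2%.

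**The case against.** The strongest case is that nothing depends on the difference. The 30 is a pilot convention, not the output of a power calculation, so no power claim for the main trial fails. The shortfall of 1.2 per arm lies well within the uncertainty of a round 20% guess: at 15% attrition, 36 × 0.85 = 30.6 would remain. The primary analysis is by intention to treat, and once more than 5% of week-4 MoCA scores are missing, "multiple imputation under a missing-at-random assumption will be used as the main ITT analysis", so all 72 would be analysed. The next trial's planners would in any case use the attrition observed here. The article also never states an expected number of completers; that 30 is meant as the number left after loss is implied. Finally, the 20% might have been meant as a margin on top of the 30, in which case 36 is correct.

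Most of this bears on size, and there it stands: the consequence is minor, and the multiplication by 1.2 is an inference, though one that fits exactly. It does not make the sentence true. An allowance for attrition added to 30 makes sense only if 30 is the number wanted after loss. Attrition is loss from those enrolled, and six lost from 36 is 16.7%. Imputation keeps all randomised participants in the analysis but does not restore unobserved week-4 scores. The Clinical data analysis section also requires an observed week-4 MoCA for the per-protocol set and relies mainly on available cases for the secondary outcomes, so the observed number matters directly there.

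**Conclusion.** The point holds. On the article's own figures, 36 per arm at 20% attrition leaves about 29 per arm, short of the stated 30 by about 1.2 per arm, or 2.4 overall. This rests on reading the 20% as a share of those enrolled and the 30 as the number wanted after loss, which are the ordinary meanings of the two sentences. It is a plain arithmetic inconsistency that should be corrected. It does not threaten the design or the primary analysis.

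**What to change.** Restate the attrition sentence in the Sample size section, for example: 36 per arm (72 in total) gives about 29 evaluable participants per arm at 20% attrition, or 30 per arm at 16.7% attrition.

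This costs one sentence. Enrolment and the total of 72 elsewhere in the article stay as they are. If the sponsor would rather keep both the 30 and the 20%, enrolment becomes 38 per arm, four more participants in total, and every mention of 72 must change. For a shortfall this small, the restatement is the proportionate choice.

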### MRI data acquisition

All MRI examinations will be performed at the MRI Center of West China Hospital, Sichuan University, on a 3.0 T scanner (Discovery MR750; GE Healthcare, Milwaukee, USA) equipped with an eight-channel phased-array head coil. Before each examination, participants will be instructed to minimize head motion, and their heads will be stabilized with foam pads. Scans will be acquired with the participant lying supine and remaining alert throughout. After acquisition, two trained neuroimaging analysts will visually inspect the magnitude and phase images for artifacts, including motion, signal dropout, and severe susceptibility distortions. Datasets with pronounced motion artifacts that preclude reliable phase unwrapping will be repeated where feasible; if repetition is not possible, the scan will be excluded from QSM analyses, and the reason will be documented.

A high-resolution structural dataset will be obtained with a three-dimensional T1-weighted spoiled gradient-echo sequence (TR/TE = 6.2/2.5 ms, field of view = 256 × 256 mm^2^, data matrix = 256 × 256, voxel size = 1.0 × 1.0 × 1.0 mm^3^). QSM will be derived from a gradient-recalled echo sequence (flip angle = 17°, field of view = 229 × 229 mm^2^, voxel size = 0.7 × 0.7 × 4.0 mm^3^, number of slices = 52, slice thickness = 4 mm).

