Statistical analysis will be performed in SPSS 26.0 (IBM, Armonk, NY, USA). Within-group changes in susceptibility (post–pre) are tested with paired-samples *t*-tests, and between-group differences are assessed with independent-samples t-tests. Pearson correlation coefficients will be calculated to examine associations between changes in ROI-based susceptibility and corresponding changes in cognitive, functional, emotional, and sleep measures; if normality is violated for either variable, Spearman’s rank correlation will be used. Data normality will be assessed with the Shapiro–Wilk test. Two-sided *p*-values of < 0.05 will be considered statistically significant, and false-discovery-rate correction will be applied across the predefined ROIs to control for type I error. Given the 4-week interval and modest imaging sample size, the QSM substudy is not powered to detect small absolute susceptibility changes. We will therefore focus on within-subject changes in ROI-based susceptibility and on medium-to-large associations with cognitive outcomes, interpreting all imaging findings as exploratory.

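### The MRI substudy's 80% power for r ≥ 0.50 fits complete pairs and one uncorrected test, not the FDR-corrected analysis that is planned

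*Protocol article*

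**What the plan says.** All references are to the protocol article.

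- **Sample size.** The substudy is drawn from the randomised patients: "we will randomly select 15 participants per arm (*n* = 30) from the clinical cohorts". The power claim, at a two-tailed α of 0.05, is that "this total sample provides approximately 80% power to detect medium-to-large correlations (r ≥ 0.50) between QSM-derived susceptibility measures and cognitive outcomes", and the method is "based on Fisher’s z transformation in G*Power 3.1". Only associations smaller than this are flagged for cautious reading.
- **Sample size, clinical arms.** "Allowing for an anticipated 20% attrition", the target of 30 per arm is raised to 36. No such allowance is made for the 30 MRI participants.
- **MRI data acquisition.** Scans too degraded by motion are repeated where feasible; "if repetition is not possible, the scan will be excluded from QSM analyses".
- **Clinical data analysis.** The MRI per-protocol set is limited to participants with usable QSM at both baseline and week 4.
- **Neuroimaging data analysis.** Eight bilateral structures are named as regions of interest (ROIs). Change in susceptibility is correlated with change in cognitive and other measures, and "false-discovery-rate correction will be applied across the predefined ROIs to control for type I error". The imaging findings as a whole are called exploratory.

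**The concern.** The power sentence rests on two conditions: a full 30 pairs, and a single test at an unadjusted 0.05. Other sections of the same article depart from both. A change score exists only if both scans are usable and the week-4 clinical measure was taken, so every dropout or rejected scan costs a pair. The false-discovery-rate (FDR) rule also means that an ROI's p-value is generally judged against a threshold below 0.05.

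What is at stake is how a null imaging result is read. The Neuroimaging data analysis section says attention will go to medium-to-large associations, and the Sample size section tells the reader that r ≥ 0.50 is covered at about 80%. If the analysis actually run has much lower power, a correlation of that size could be missed far more often than one time in five.

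**Working it through.** **Inputs.** From the article: r = 0.50, n = 30, two-sided α = 0.05, Fisher's z, 20% attrition (stated for the clinical sample), eight bilateral ROIs, FDR across ROIs.

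Assumptions, because the article does not give them:
- FDR is applied by the Benjamini–Hochberg (BH) procedure at 5%.
- The number of tests is 8 if left and right are averaged, 16 if they are kept apart.
- The number of ROIs truly associated at r = 0.50 is varied from one to all.
- For the loss scenario, the clinical 20% applies to the substudy.

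**Step 1: reproduce the stated figure.** Power = Φ(atanh(r)·√(n−3) − z₁₋α/₂), with a negligible opposite tail.
- atanh(0.50) = 0.5493 and √27 = 5.196, product 2.854.
- Φ(2.854 − 1.960) = Φ(0.894) = 81.4%. The stated figure reproduces.
- Sample size for exactly 80%: ((1.960 + 0.842)/0.5493)² + 3 = 29.01. Power is 80.0% at n = 29 and 78.4% at n = 28.

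**Step 2: loss only.** n = 30 × 0.80 = 24.
- 0.5493 × √21 = 2.517; Φ(2.517 − 1.960) = Φ(0.557) = 71.1%.
- The step from 36 to 30 per arm is a loss of 6/36 = 16.7%, which would leave 25 pairs and 73.1%.

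**Step 3: the first BH step.** The smallest of m p-values is compared with 0.05/m. If only one ROI is associated, this threshold largely decides the result.

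| Pairs | α = 0.05 | 0.05/8 | 0.05/16 |
|---|---|---|---|
| 30 | 81.4% | 54.8% | 46.0% |
| 24 | 71.1% | 41.4% | 33.1% |

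Critical values are 1.960, 2.734 and 2.955.

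**Step 4: the full BH procedure.** When several ROIs are associated the threshold relaxes, so BH was simulated. The entries are the average power per truly associated ROI, with bivariate normal data and ROIs independent given the cognitive score.

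| Pairs | Tests | One associated | Half | All |
|---|---|---|---|---|
| 30 | 8 | 56% | 70% | 80% |
| 30 | 16 | 47% | 70% | 80% |
| 24 | 8 | 42% | 56% | 67% |
| 24 | 16 | 33% | 54% | 66% |

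These carry simulation error of about a point. A residual correlation of 0.5 between ROIs changes them by at most about three points (for example, 77% to 78% in place of 80% with all associated and 30 pairs).

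**Step 5: the correlation detectable with 80% power at n = 24.** r = tanh((z₁₋α/₂ + 0.842)/√21).
- α = 0.05: tanh(2.802/4.583) = 0.545.
- α = 0.05/8: tanh(3.576/4.583) = 0.653.

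**The case against.** The best defence is that the sentence states its conditions and is correct under them. It names n = 30, α = 0.05 and the method, and it does not claim to cover attrition or FDR. Quoting power per test at a nominal level is common in an exploratory substudy, and the article repeatedly calls the imaging work preliminary. This stands to the extent that a reader who inferred a calculation error would be wrong.

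Several other objections also hold:
- The 20% is given for the clinical sample. There is no separate MRI loss rate, motion-degraded scans may be repeated, and the both-visits rule defines the MRI per-protocol set. Twenty-four pairs is therefore an assumption, not the plan's own forecast.
- It is too strict to say that all 30 pairs are needed, since 29 still give 80.0%.
- The lowest figure, 33%, needs three things together: 24 pairs, 16 separate tests and one associated ROI. The article supports none of these specifically. The ROIs were all chosen as plausible, and if all are associated with no loss, power is close to 80%.
- A reader might infer that future trials will be sized from this power figure. The Sample size section says they will be guided by estimates of effect size and variance.

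The defence does not remove the mismatch. The power figure, the attrition allowance and the FDR rule all appear in the same article. The exploratory label does not tell the reader that the 80% belongs to a different test. Even with no loss at all, FDR takes power to between 47% and about 70% when half the ROIs or fewer are associated.

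**Conclusion.** The concern holds as a mismatch between the power statement and the planned analysis. About 80% is right for 29 to 30 complete pairs and one uncorrected test. For the FDR-corrected analysis with no loss, it is about 56% (8 tests) or 47% (16 tests) if one ROI is associated, about 70% if half are, and about 80% only if all are. With 24 pairs, it is 71% before FDR and about 33% to 67% after. The 71% reflects loss alone and should not be read as the upper end once loss and FDR act together.

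The FDR result depends on the number of tests and of associated ROIs, which the article leaves open. The loss result depends also on carrying the clinical 20% over to the substudy. The consequence is limited to the reading of exploratory imaging correlations; the sole primary endpoint, MoCA change at week 4, is not touched.

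**What to change.** Change one sentence in the Sample size section, in either of two ways:

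1. Restate power for the number of analysable pairs expected and for the FDR-corrected test, naming the assumed loss, the number of tests and the number of associated ROIs. For example, with 24 pairs, 80% power is reached at r of about 0.55 for a single unadjusted test, and at about 0.65 at the 0.05/8 threshold.
2. Keep the 80% and label it as power per ROI, without multiplicity correction and with complete data on all 30.

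The first is more informative because it describes the analysis that will be reported. Neither needs additional patients or scans. The only cost is a less favourable figure or a visible qualification.
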